### Timetable

Timetable and visit plan are outlined in Fig. 1.

**Fig. 1 Fig1:**
[figure not shown]
Visit plan. Detailed itemization of planned follow-ups and actions taken

### Surface electrical stimulation

After a guideline-dependent decision of the initial treatment for LDH, patients will be randomized into two groups, respectively, in a 1:1 allocation ratio: 20 patients (50%) in Population 1 and 20 patients (50%) in Population 2 will receive SES, whereas the other half will follow standardized treatment algorithms adjusted to the initially chosen therapy for LDH (see Additional file 3: Figure S1).

Stimulation is initially applied within three days post intervention. Patients are trained by the clinical investigator(s) at the study site to ensure proper usage of the stimulation device. Patients are then requested to perform treatment at home. Five electrodes (4 × 6.4 cm PALS latex-free neurostimulation electrodes, model 896230) are placed on the skin in the affected nerve root distribution area L3 to S1, according to instructions documented in the patient’s individual manual. For better comparability, standardized characteristic muscles for each nerve root are chosen for stimulation. M. quadriceps femoris covers distribution areas of the roots L3 and L4, M. tibialis anterior covers L5, and M. gastrocnemius is innervated by S1. Four electrodes are used to cover an as wide as possible area of each muscle, the fifth electrode is used for reference of the EMG capacity and is closely placed to bony structure (femur condyles or ankle) (see Additional file 4: Figure S2). The electrode surface of 25.6 cm^2^was chosen according to the volume of the stimulated muscles. The stimulation device (STIWELL med4, MED-EL) is started and the pre-set program (pulse width = 300 μs, frequency = 30 Hz, plateau time = 8 s, pause time = 16 s, rise time = 2 s, fall time = 2 s) is chosen. This program was developed with STIWELL specialists in the field of clinical rehabilitation and was adjusted on the condition’s special indications and expectations of recovery. The intensity will be increased until the patient feels and sees muscle contraction. If motor habituation appears, patients are instructed to increase the intensity until the comfortable tingling sensation and/or muscle contraction can be seen again. EMG triggers are imparted over the devices’ display and clearly signal the patient when to actively tense her/his muscles and when to pause. Thresholds for the EMG trigger are set at the maximum amount of electrical activity the patient is able to create. The device is set on automatic mode, which adjusts the threshold up after a successful trial or regulates it down after an unsuccessful one. Patients are instructed to perform this treatment for 1 h daily (2 × 30 min) for the following eight weeks. Time, date, and duration of each treatment should be noted in a provided document and handed out to the investigators at the next follow-up. Furthermore, treatment time, duration, and EMG thresholds can be read out directly from the device to surveil the patient’s compliance. If the treatment is conceived uncomfortable or skin irritation appears, patients are requested to immediately contact the clinical investigators.

### Sequestrectomy

Surgery is performed after induction of general endotracheal anesthesia and with the assistance of an operating microscope, while the patient is in a prone position. Surgery is performed by two trial designated surgeons in a standardized manner. The spinal canal harboring the sequestrated disc material is exposed by performing a minimal inter-laminar fenestration to avoid removal of bone and articular structures. Based on results of a previous trial, only the herniated material is removed. The herniated space is not entered whenever possible [1, 31].

### Randomization

The allocation ratio within groups is 1:1 (see Additional file 3: Figure S1). The randomization code will be generated independently from the clinical investigators according to a random permuted blocks method with varying block size. Statistical Software Stata 10.0 module Ralloc version 3.5.2 (Statacorp College Station, TX, USA) will be used to generate the random code. An independent statistician will administer the randomization code.

### Data management

Study data generation done by the clinical investigators ([name]) at the study site (Department of Neurosurgery) and data storage, processing, and statistical analysis performed by the cooperating partners (SN) at the Department of Medical Statistics, Informatics and Health Economics are clearly separated. A validated database system programmed in a customized software package, which is provided by the Department of Medical Statistics, Informatics and Health Economics, is available. The evaluation of the data takes place by double-entry of the data and manual/visual evaluation of plausibility. After entry of all collected data and clarification of all queries, the database will be closed at the completion of the study.

### Sample size calculation

Sample size calculation is based on the primary endpoint of the study, the cold detection threshold (CDT) two years post intervention. Relevant data were acquired from previous prospective trials at our center, also using the CDT as a primary outcome parameter. Sixty-three patients are required to detect a difference of 3.4 considering a standard deviation (SD) of 6.8 with 80% power on a two-sided level of significance of 0.05. We considered a loss to follow-up < 20% adequate for final calculation of sample size, which is 75–80 patients.

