**Methods/Design:**

This is a prospective, monocentric, randomized, controlled clinical trial. A total of 80 adult patients suffering from a lumbar disc herniation (LDH; 40 treated surgically, 40 conservatively) are allocated in a ratio of 1:1. Patients in the treatment group will receive surface electromyography (EMG)-triggered electrical stimulation for eight weeks, whereas patients in the control group will not obtain any additional treatment. The primary outcome parameter is defined as the cold detection threshold (CDT), determined by quantitative sensory testing (QST), 24 months after intervention. Secondary outcome parameters include the inquiry of sensory nerve function by two-point discrimination and QST, the assessment of motor nerve function by manual muscle testing, and validated scales and scores. These include: the Oswestry Disability Index (ODI) and the Core Outcome Measures Index (COMI) assessing the domains pain, back-specific function, work disability, and patient satisfaction; the EQ-5D investigating the patient’s generic health status; the painDETECT questionnaire (PD-Q) to identify neuropathic pain components; and the Beck Depression Inventory (BDI) to assess severity of depression. Moreover, neurological status, pain medication usage, and blood samples (CRP, TNFα, IL-1β, IL-6) will be evaluated. Study data generation (study site) and data storage, processing, and statistical analysis are clearly separated.

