### Statistical analyses

All statistical analyses will be performed in consultation with the Department of Medical Statistics and Health Economics, Innsbruck Medical University, Innsbruck, Austria. Detailed descriptive statistics will be provided for the data collected and 95% confidence intervals will be calculated for all relevant estimates. The primary analysis will follow as the randomized principle. All patients with a complete pre-treatment examination will be considered for inclusion into the population. Primary outcome parameter will be the CDT. We estimate that the 24 months change of the CDT in patients treated without SES will be approximately 10%, whereas patients treated with SES should show a better improvement up to 20% of the initial threshold. In a one-way analysis of variance (ANOVA) test, group sample sizes of 35 patients in each group achieve 80% power to detect a significant difference between the CDT estimates with an estimated standard deviation of 20%. To adjust for multiple pairwise comparisons, the critical *p* value for statistical significance was adjusted to *p* ≤ 0.05. Descriptive analyses will include reporting means (with SDs) for continuous variables and frequencies (with percentages) for discrete variables. One-way analysis of variance (or non-parametric Kruskal–Wallis equivalent) will be used to assess the difference in the primary outcome of CDT between those patients that received conventional therapy (without SES) and those who received SES. Differences between each patient, compared to the not affected body site, will be analyzed using paired t-test to adjust for the clustered nature of the thresholds for each patient.

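### Enrolment and evaluable numbers disagree: the lower end of 75–80 falls short of 63 at 20% loss, and 80 enrolled gives 35 per group only if loss is at most 12.5%

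*Protocol article*

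**What the plan says.** The protocol article gives sample-size figures in four places.

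- **Sample size calculation, requirement:** "Sixty-three patients are required to detect a difference of 3.4 considering a standard deviation (SD) of 6.8". Power is set at 80% and the two-sided alpha at 0.05.
- **Sample size calculation, attrition:** "We considered a loss to follow-up < 20% adequate for final calculation of sample size, which is 75–80 patients".
- **Statistical analyses:** a second calculation, with a 10% change without stimulation, 20% with it and an SD of 20%, concludes that "group sample sizes of 35 patients in each group achieve 80% power to detect a significant difference between the CDT estimates".
- **Abstract, Methods/Design:** "A total of 80 adult patients suffering from a lumbar disc herniation (LDH; 40 treated surgically, 40 conservatively". The Surface electrical stimulation section matches this: 20 patients from each population receive stimulation and the other half do not, so 40 per arm when the populations are pooled.

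The loss allowance is attached only to the 63. No enrolment figure is derived from the 35 per group.

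**The concern.** The primary endpoint is read at 24 months, so attrition decides how many patients are analysed. A plan that names a required evaluable number, a tolerated loss and an enrolment target should have the three agree. Here there are two evaluable requirements (63 and 70) and two enrolment statements (a range of 75–80 and a fixed 80), and they are not reconciled. If the lower end of the range were used, the trial could keep its loss within the level it calls adequate and still analyse fewer patients than either calculation asks for. Readers would also take 35 analysed per arm, with 80% power, as what the design delivers.

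**Working it through.** **Inputs.** Difference 3.4, SD 6.8, 80% power, two-sided 0.05, 63 required, loss below 20%, enrolment 75–80 (all from Sample size calculation); 35 per group, difference 20% − 10% = 10 points, SD 20% (Statistical analyses); 80 enrolled, 40 per arm (Abstract; Surface electrical stimulation). Both calculations have the same standardised effect: 3.4/6.8 = 0.5 and 10/20 = 0.5.

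**The plan's own figure.** For two means, n per arm = 2 × (1.96 + 0.84)² / 0.5² ≈ 62.8, so 63 **per arm**, or 126 in total (exact t: 64 per arm, 128 in total). The article carries 63 forward as a total, since 75–80 cannot be reached otherwise. The attrition check below takes 63 and 35 at face value.

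**Attrition for 63.** Enrolled = evaluable / (1 − loss).

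- 63 / 0.80 = 78.75, so 79.
- 75 × 0.80 = 60, below 63.
- 80 × 0.80 = 64, above 63.
- Largest loss that keeps 63: 1 − 63/75 = 16.0%; 1 − 63/80 = 21.25%.

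The text says below 20%, so the same check in whole patients:

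| Enrolled | Lost | Loss | Left |
|---|---|---|---|
| 75 | 13 | 17.3% | 62 |
| 75 | 14 | 18.7% | 61 |
| 76 | 15 | 19.7% | 61 |
| 77 | 15 | 19.5% | 62 |
| 78 | 15 | 19.2% | 63 |
| 80 | 15 | 18.75% | 65 |

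Under the strict wording, totals of 75, 76 and 77 can fall short of 63; 78 and above cannot.

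**Attrition for 35 per group (70), read as analysed patients.**

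- 70 / 0.80 = 87.5, so 88.
- 80 × 0.80 = 64, or 32 per arm if loss is even. In whole patients, any loss of 11 to 15 out of 80 (13.75% to 18.75%) is below 20% and leaves 69 to 65.
- Largest loss that keeps 70: 1 − 70/80 = 12.5%; 1 − 70/75 = 6.7%.

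**What these numbers deliver.** Two-sided 0.05, standardised effect 0.5, normal approximation Φ(0.5 × √(n/2) − 1.96), with the two-sample t result beside it:

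| n per arm | Normal | t |
|---|---|---|
| 30 | 0.49 | 0.48 |
| 32 | 0.52 | 0.50 |
| 35 | 0.55 | 0.54 |

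Expected 95% interval at 32 per arm with SD 6.8: standard error 6.8 × √(2/32) = 1.70; half-width about 2.0 × 1.70 = 3.4, the same size as the difference to be detected.

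**The case against.** The best defence is that 80 is the operative number. The abstract states it, the allocation of 20 per cell implies it, and 64 remaining is more than 63. That stands: the shortfall against 63 concerns only the lower end of the range. A reader might infer that the trial will stop at 75, or that its planned enrolment misses 63. The article supports neither; it describes no stop at 75.

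Second, nowhere is 35 per group said to be the number after dropout, and the loss allowance belongs to the other calculation. This is fair, so the 12.5% limit and the 32-versus-35 gap depend on reading 35 as analysed patients. That is the natural reading, because the sentence ties 35 to achieved power. Reading it as enrolled gives 70, which contradicts both 75–80 and 80, so some inconsistency remains either way.

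Third, it is tempting to say that the range came from multiplying by 1.2 (63 × 1.2 = 75.6) instead of dividing by 0.8. The article does not show how the range arose, and the correct 79 lies inside it. The cause is conjecture; the shortfall at 75 is not.

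Finally, attrition moves power by only 4 to 6 points (0.54 to 0.50 or 0.48), while 35 per group already falls about 26 points short of the claimed 80%. That is correct and limits the weight of this point. A reader might also infer that enrolling 79 or 88 would restore 80% power. It would not under the stated two-group comparison, whose inputs give 126 to 128 evaluable, or 158 to 160 enrolled at 20% loss. A baseline-adjusted analysis could need fewer, but the article states no baseline correlation and names a one-way ANOVA.

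**Conclusion.** The point holds as an inconsistency among the article's own figures. Totals of 75 to 77 do not protect 63 evaluable patients at the loss called adequate; 80 does. If 35 per group means patients analysed, 80 enrolled secures it only up to 12.5% loss, and at 20% about 32 per arm remain. These sums assume 1:1 arms pooled over both populations, even loss, and the stated 63 and 35 taken at face value. Neither figure gives 80% power as used: 63 is the per-arm result of its inputs, and 35 per arm gives about 0.54. That is the larger defect. The attrition mismatch is a secondary correction, worth making because it is cheap and because the text as it stands is wrong.

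**What to change.** 1. In Sample size calculation, drop the 75 and give enrolment as 80, as in the abstract.
2. State one expected evaluable number in both Sample size calculation and Statistical analyses: 64 in total, 32 per arm, at 20% loss.
3. Remove the 80% power claim attached to 63 and to 35 per group. Give instead the power at the stated standardised effect of 0.5 (about 0.50 two-sided at 32 per arm; about 0.54 at 35), or the expected interval half-width (about 3.4 at 32 per arm with SD 6.8). Do not simply put 32 in place of 35 in the existing sentence, which would make it less true.
4. Make the change together with the correction of 63 from a total to a per-arm figure. If the sample size itself is then revised, recompute enrolment by dividing by one minus the loss.

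The cost is wording in two sections and a less favourable stated power. Making the statements agree needs no extra patients; reaching 80% power would be a separate decision.

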### Statistical analyses

All statistical analyses will be performed in consultation with the Department of Medical Statistics and Health Economics, Innsbruck Medical University, Innsbruck, Austria. Detailed descriptive statistics will be provided for the data collected and 95% confidence intervals will be calculated for all relevant estimates. The primary analysis will follow as the randomized principle. All patients with a complete pre-treatment examination will be considered for inclusion into the population. Primary outcome parameter will be the CDT. We estimate that the 24 months change of the CDT in patients treated without SES will be approximately 10%, whereas patients treated with SES should show a better improvement up to 20% of the initial threshold. In a one-way analysis of variance (ANOVA) test, group sample sizes of 35 patients in each group achieve 80% power to detect a significant difference between the CDT estimates with an estimated standard deviation of 20%. To adjust for multiple pairwise comparisons, the critical *p* value for statistical significance was adjusted to *p* ≤ 0.05. Descriptive analyses will include reporting means (with SDs) for continuous variables and frequencies (with percentages) for discrete variables. One-way analysis of variance (or non-parametric Kruskal–Wallis equivalent) will be used to assess the difference in the primary outcome of CDT between those patients that received conventional therapy (without SES) and those who received SES. Differences between each patient, compared to the not affected body site, will be analyzed using paired t-test to adjust for the clustered nature of the thresholds for each patient.

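### The primary endpoint is a 24-month CDT value in two sections, but is planned as percent change from baseline in a third, and the analysed form and baseline adjustment are left open

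*Protocol article*

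**What the plan says.** Abstract, Methods/Design: "The primary outcome parameter is defined as the cold detection threshold (CDT), determined by quantitative sensory testing (QST), 24 months after intervention". This is a value at a time point.

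Sample size calculation: the basis is "the primary endpoint of the study, the cold detection threshold (CDT) two years post intervention". The figures are "Sixty-three patients are required to detect a difference of 3.4 considering a standard deviation (SD) of 6.8 with 80% power"; the test is two-sided at the 5% level. No unit is given for 3.4 and 6.8.

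Statistical analyses: the outcome is again called simply the CDT, but the planning assumptions are relative to baseline. For the control arm: "We estimate that the 24 months change of the CDT in patients treated without SES will be approximately 10" percent. For the SES arm: "patients treated with SES should show a better improvement up to 20% of the initial threshold". The power statement takes 35 patients per group and 80% power, "with an estimated standard deviation of 20" percent. The arms are then to be compared on CDT by one-way ANOVA or its Kruskal–Wallis counterpart. That sentence does not say which form of CDT enters the test, and it has no baseline covariate. ANCOVA appears in the Abbreviations list and nowhere else in the article.

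**The concern.** A threshold measured at 24 months and a change expressed as a percentage of the starting threshold are different variables. Each has its own planning figures and its own power statement here, and no sentence connects them. If the analysed form is not fixed, value, absolute change and percent change all remain available. They can give different p values from the same data, so the choice could be made after the data are seen.

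Percent change is also an awkward scale for a thermal threshold. If CDT is recorded as a temperature, the percentage depends on where the temperature scale has its zero. If it is recorded as distance from a start temperature, patients with small baselines give unstable ratios. The article does not say which recording is used.

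**Working it through.** **Inputs.** From the Sample size calculation section: difference 3.4, SD 6.8, two-sided 0.05, 80% power. From the Statistical analyses section: 10% against 20% (the top of the stated range for SES), SD 20%, 35 per group. The baseline-to-24-month correlation r, the mean baseline CDT, the unit and the start temperature are not in the article; any value used for them below is an assumption.

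**1. The plan's own figures.**
- Standardised difference: 3.4/6.8 = 0.50 and (20 − 10)/20 = 0.50.
- n per arm = 2 × (1.960 + 0.842)² / 0.50² = 62.8, so 63 per arm (126 in total). The stated 63 is reproduced only as a per-arm number; split 32 and 31, it gives about 50% power.
- With 35 per group, 0.50 × √(35/2) − 1.960 = 0.13, so power is about 55% (54% by the t or F test), not 80%.

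Both scales have the same standardised difference, so the mismatch of scales does not explain the power error.

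**2. When would the two sets describe the same thing?**
- 3.4/0.10 = 34 and 6.8/0.20 = 34, so the mean baseline must be near 34 in the unstated unit.
- With equal variances, the SD of change is SD × √(2(1 − r)). It equals the SD of the 24-month value when r = 0.5.

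Neither condition is stated.

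**3. How far does the 20% SD depend on the baseline?** Illustrative simulation, 400,000 draws per row. Assumptions: normal baseline with SD 6.8, r = 0.5, equal variances, follow-up mean 10% lower than baseline, baselines of 0.5 or less dropped.

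| Mean baseline | Mean percent reduction | SD of percent reduction (points) |
|---|---|---|
| 34 | 8.1 | 21 |
| 20 | 1.8 | 64 |
| 15 | −5.3 | 106 |
| 10 | −10.7 | 163 |

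The planned SD is roughly met at 34. At lower baselines the SD rises steeply and the mean drifts from the true 10% reduction. The rows with low baselines depend on the cut at 0.5, so they show the instability rather than a usable value.

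**4. Dependence on the zero point.** For threshold T and start temperature S, a 10% change is 0.10 × T on the absolute scale and 0.10 × (S − T) on the distance scale, a ratio of T/(S − T). With S assumed to be 32, the ratio is 1.7 at T = 20, 3 at 24, 7 at 28 and 15 at 30. No single ratio can be attributed to this trial.

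**5. Gain from adjusting the 24-month value for baseline.** Relative to the unadjusted value, under equal variances, the variance factor is 1 − r², and n per arm = 62.8 × (1 − r²).

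| Assumed r | Variance factor | n per arm, ANCOVA |
|---|---|---|
| 0 | 1.00 | 63 |
| 0.3 | 0.91 | 58 |
| 0.5 | 0.75 | 48 |
| 0.7 | 0.51 | 33 |

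With 80 randomised and 20% lost, 32 per arm remain. ANCOVA then reaches 80% power only if r is about 0.70 or more, since 62.8 × (1 − r²) = 32 gives r = 0.70.

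**The case against.** The strongest reply is that the article never names percent change as the primary variable. Every sentence that names the outcome says CDT; the percentages appear only in a planning estimate and the power sentence. That stands. A reader might infer that two primary analyses with two different tests are prescribed. The article does not support this: the Sample size calculation section names no test, and the Statistical analyses section names one approach for the arm comparison. What is left open is the variable that goes into it.

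It can also be said that both ratios equal 34, so this may be one assumption written twice. That is possible, and it rules out the reading that the figures agree only if every patient starts at 34: with baselines varying by SD 6.8 around a mean of 34, the simulated SD is still about 21 points. But the article gives no mean baseline and no unit, so a reader cannot confirm it.

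A reader might further infer that percent change costs 33% more patients. The documents do not support that. The figure is 1/0.75, the gain from baseline adjustment at an assumed r of 0.5, where simple change has the same variance as the unadjusted 24-month value. It is an argument for the covariate and does not measure a loss from percent change.

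Finally, value versus change and the choice of covariates are often left to an analysis plan, and the ANCOVA abbreviation suggests that adjustment may have been intended. Silence alone would be no finding. Here, however, the article itself sets out two planning scales for one endpoint, and condensation does not account for that.

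**Conclusion.** The point holds as an inconsistency in how the primary variable is fixed. Two places make it the 24-month CDT value, a third plans and powers on percent change from baseline, and the analysis sentence does not settle which form is tested. The figures can be reconciled only under conditions that the article does not state.

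The objection to percent change is a methodological judgement that holds for either recording of CDT, though for different reasons; how severe it is here cannot be sized without the unit and the baseline distribution.

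The gain from adjusting the 24-month value for baseline is a variance factor of 0.91 to 0.51 for r from 0.3 to 0.7. It rests on equal variances and on an assumed r. It should not be read as rescuing the sample size: a standardised difference of 0.5 needs about 63 per arm unadjusted, 35 per group gives about 54–55% power, and that error must be dealt with separately.

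**What to change.** Use one definition in the Abstract, the Sample size calculation and the Statistical analyses sections: CDT of the affected side at 24 months, in its recorded unit, with a statement of whether it is an absolute temperature or a distance from a start temperature. Compare the arms by ANCOVA with baseline CDT as covariate. Say that baseline means the examination before randomisation, because the Discussion also mentions a pre-operative QST as a reference for patients who cross over. Keep percent change as a descriptive summary only.

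State the planning figures once, on that scale and with the unit. If the calculation takes credit for the covariate, state r with its source (the centre's previous trials with CDT as primary outcome are an obvious place to look) and show a range.

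No new data are needed: inclusion in the analysis population already requires a complete pre-treatment examination. The cost is rewording plus one restated calculation. Correcting the group sizes or the power claim is a further step with its own cost.

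### The stated 80% power for 35 patients per group does not follow from the stated inputs: the named two-group ANOVA has about 54%, and 80% needs 64 per group

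*Protocol article*

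**What the plan says.** The Statistical analyses section contains a complete power statement on the percent-change scale.

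- **Control group:** the "24 months change of the CDT in patients treated without SES will be approximately 10" per cent.
- **SES group:** "patients treated with SES should show a better improvement up to 20% of the initial threshold".
- **Variability:** "with an estimated standard deviation of 20" per cent.
- **Claim:** in a one-way ANOVA, "group sample sizes of 35 patients in each group achieve 80% power to detect a significant difference between the CDT estimates".
- **Significance level:** "the critical *p* value for statistical significance was adjusted to *p* ≤ 0.05".
- **Analysis:** "One-way analysis of variance (or non-parametric Kruskal–Wallis equivalent) will be used to assess the difference in the primary outcome of CDT", the comparison being "between those patients that received conventional therapy (without SES) and those who received SES".

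The Sample size calculation section gives another calculation on the raw CDT scale: a difference of 3.4, an SD of 6.8, 80% power, two-sided 0.05, and 63 patients. It ends: "We considered a loss to follow-up < 20% adequate for final calculation of sample size, which is 75–80 patients". The Abstract and the Surface electrical stimulation section put the total at 80, with 20 of the 40 patients in each treatment population receiving SES. That makes 40 against 40 for the primary comparison.

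**The concern.** A difference of 10 points on an SD of 20 is half a standard deviation. A two-group comparison of that size needs more than 60 patients per group for 80% power, so 35 per group looks too small at sight.

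This is the only power claim in the article that is tied to the named primary test and to the percent-change scale. If it is wrong, readers are told that the trial would miss the planned effect in two of ten repetitions, when the figure is between four and five. Correcting only the 63-patient figure would leave this sentence as apparent independent support for 80% power. A non-significant result could then carry more weight against SES than the design can bear.

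**Working it through.** **Inputs (Statistical analyses section unless noted)**
- Changes of 10% and 20%, so a difference of 10 points.
- SD 20, so d = 10/20 = 0.5 (ANOVA f = 0.25).
- Two groups of 35, level 0.05. The two-sided level is taken from the Sample size calculation section.

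**Attempt to reproduce the stated figure**

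With two groups, one-way ANOVA is the two-sided two-sample t-test. The noncentrality parameter is d·√(n/2) = 0.5 × √17.5 = 2.09. The critical t on 68 degrees of freedom is 1.995. The noncentral t (equivalently noncentral F) distribution gives a power of **54.1%**; the normal approximation gives 55.2%. The stated 80% is not reproduced.

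**Group size needed for 80%**

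Normal approximation: n = 2(1.960 + 0.842)²/0.5² = 62.8, so 63 per group. The t-test gives 63.8, so **64 per group**, or 128 evaluable patients.

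**What would make 35 per group correct**

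With 35 per group, 80% power requires d = 0.679. That means a difference of 0.679 × 20 = 13.6 points at SD 20, or an SD of 10/0.679 = 14.7 at a difference of 10 points.

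**Other readings of the sentence**

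| Reading | Power |
|---|---|
| One-sided 0.05, 35 per group | 66.5% |
| Two-sided 0.10, 35 per group | 66.5% |
| Two-sided 0.025, 35 per group | 42.5% |
| Kruskal–Wallis, 35 per group (relative efficiency 0.955 under normality) | about 52% |
| Three-group ANOVA, 35 per group (10, 10, 20) | 55.8% |
| Four-cell ANOVA, 35 per cell (10, 20, 10, 20) | 68.4% |
| 35 in each of four cells, pooled to 70 v 70 | 83.6% |

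The last two rows need 4 × 35 = 140 patients, against 80 planned.

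**Power within the planned enrolment (d = 0.5, two-sided 0.05)**

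| Evaluable per group | How it arises | Power for 10 points | Difference with 80% power |
|---|---|---|---|
| 40 | 80 patients, no loss | 59.8% | 12.7 points |
| 35 | 80 patients, 12.5% loss (80 × 0.875 / 2) | 54.1% | 13.6 points |
| 32 | 80 patients, 20% loss (80 × 0.8 / 2) | 50.4% | 14.2 points |
| 30 | 75 patients, 20% loss (75 × 0.8 / 2) | 47.8% | 14.7 points |

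**Comparison with the other calculation**

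3.4/6.8 is also 0.5. With the same standardised difference, level and power, one section arrives at 63 patients and the other at 35 per group, or 70. The 63 equals the normal-approximation size for one group.

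**The case against.** The arithmetic is hard to dispute, so the best case on the other side concerns its cause, its independence and its weight.

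- **A different formula may have been used.** A one-sample or paired t-test with d = 0.5 needs 34 patients for 80% and has 82% power at 35, so a reader might infer that a paired formula was applied by mistake. The article does not say so, and the match is near rather than exact. A shared origin with the 63-patient figure is also possible: 63 taken as a total and divided by 0.9 gives 70, which is 35 per group. The 10% allowance there is an assumption not found in the article. Neither explanation can be established.
- **Baseline adjustment could rescue the number.** Adjusting for a baseline value correlated at about 0.68 with the outcome would give 80% with 35 per group. The power sentence names a one-way ANOVA and states no correlation or covariate. ANCOVA appears only in the abbreviation list.
- **It is the same shortfall as in the Sample size calculation section.** Both sections rest on d = 0.5, and enrolment is derived there, not here. This stands as a reason to correct the two together. It does not make the sentence right.
- **Attrition does not contradict the 35.** A reader might infer that the plan cannot deliver 35 per group. The 20% is a ceiling, and a 12.5% loss from 80 leaves exactly 35. The 30 and 32 per group are ceiling-loss cases only.
- **Misreading of a null result is not certain.** The plan already promises 95% confidence intervals for relevant estimates, which limits the harm.

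**Conclusion.** The power statement is wrong as written. For the named two-group test with the stated inputs, 35 per group gives about 54% power rather than 80%, and 80% needs 64 per group. No standard two-group reading that fits 75–80 patients reaches 80%; the range is about 48% to 60%.

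This rests on a two-sided 0.05 level, an SD of 20 points for the quantity analysed, equal groups, and no covariate adjustment, all as stated or implied in the article. It takes the full 10-point difference. Because the SES change is given as a maximum, a smaller true difference would lower the power further.

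The conclusion does not depend on how the error arose, and the article does not allow that to be determined.

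**What to change.** Keep the enrolment. In the Statistical analyses section, delete the 80% claim for 35 per group and state what the named test delivers, for example:

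> With 30–40 evaluable patients per group, SD 20% and two-sided alpha 0.05, the power for a 10-point difference is 48–60% (54% at 35 per group). The difference detectable with 80% power is 12.7–14.7 points (13.6 at 35 per group).

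Correct the 63-patient figure in the Sample size calculation section at the same time, and use the same evaluable number per group in both sections. Add that a non-significant result does not by itself exclude a 10-point benefit and will be read from the 95% confidence interval already planned.

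The cost is rewording and a less favourable stated power, with no extra patients or procedures. The rewording discloses the shortfall but does not remove it: 80% power for 10 points with this test would still need 64 evaluable patients per group.
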